#### Healthy facility assessment and core model checklist

The Health Facility Assessment will be analyzed to determine proportion of sites meeting the standards for signal functions and staffing, and the Core Model Checklist will be analyzed to determine the proportion of sites meeting Core Model domain requirements. Data will be stratified by intervention and control as well as district/province and compared over time.

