## Methods/Design

### Aim and objectives

The overall aim of this study is to generate evidence on the implementation effectiveness and sustainability of the MAHMAZ project and reasons for variation in order to inform the interpretation of the outcomes of the main trial. The specific objectives of our study include:
To assess the degree to which each intervention component is implemented according to the project plan and to document any adjustments and/or adaptations.To identify barriers and facilitators to implementation of the intervention components.To assess the extent to which implementation of the Core Model is perceived as responsive to community standards of acceptability by both the community and the women compared to the standard of MWH care at control sites.To assess the ways in which health facility-level factors change over the course of implementation in MAHMAZ sites compared to control sites, both during the intervention and after direct external support has ended.To assess the ways in which service utilization patterns at both MWH and rural health centers change over time in MAHMAZ sites compared to control sites both during the intervention and after direct external support has ended.To develop a contextual history of other factors that may influence both the implementation and the outcomes at the community, district, provincial and national levels.To identify key features of the entrepreneurial strategies and management models developed to support MWH operations, and assess their immediate and sustained effectiveness.

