### Study setting

The MAHMAZ cRCT is taking place in three districts in the Southern Province (Choma, Kalomo, and Pemba) and one district in Eastern Province (Nyimba) of Zambia. All study districts are primarily rural. Choma district has a total population of 247,860, with 76% living in rural areas. Kalomo, which has the largest rural population in Southern Province, has a total population of 258,570, with about 93% living in rural areas [20]. During the 2010 census Pemba was part of Choma district. Nyimba district has a total population of 77,359, with 91% living in rural areas [21].

A total of 22 health facilities in the districts were eligible for the intervention based on criteria to ensure a basic level of quality, including transfer time to nearby facilities that provide comprehensive emergency obstetric and newborn care (2 h or less), delivery volume (≥150 per year), and either 1) the ability to perform basic emergency obstetric and newborn care (BEmONC) signal functions (five out of seven), which are a set of interventions to care for the mother and newborn during intrapartum care [22] or 2) had at least one skilled attendant on staff, routinely practices active management of third stage of labor, and had no stock outs of oxytocin or magnesium sulfate in the preceding 12 months. The 20 facilities farthest from the referral hospital were selected and matched into pairs based on travel time to referral hospital and delivery volume. Pairs were then randomly assigned to the intervention or control group. Detailed information about the setting, randomization process, and selection criteria can be found in the trial protocol [10]. MWHs were also constructed at two of the five main referral hospitals in the study districts. The MWHs at referral hospitals do not include all of the intervention elements of the Core Model. They are being assessed separately and therefore are not detailed in this implementation protocol.

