### Study design and conceptual framework

We will use a mixed-methods approach and collect longitudinal, cross-sectional data at both the MAHMAZ intervention rural health center sites (*n* = 10) and the matched control sites (n = 10) before and during MAHMAZ project implementation, and for a short period (approximately 4 months) after cessation of project support.

Our study is guided by an integrated framework drawing from the Consolidated Framework for Implementation Research (CFIR) by Damschroder et al [19] and the Conceptual Framework for Sustainability of Public Health Programs (the Sustainability Framework) put forward by Scheirer and Dearing [18]. CFIR synthesizes constructs from multiple key implementation frameworks that are hypothesized to influence implementation. The Sustainability Framework posits the relationships between factors affecting sustainability and sustainability outcomes within a broader socio-political environment. Because these frameworks address different but related key drivers of program success – implementation and sustainability – elements from each underpin our study. We discuss these frameworks in more detail in the analysis section below.

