**Fig. 1 Fig1:**
[figure not shown]
Routine implementation data by category

**Table 2 Tab2:** Objectives, Questions, Data Sources for the MAHMAZ Implementation Effectiveness Protocol

Objective	Evaluation Questions	Data Sources
1. To assess the degree to which each individual intervention is effectively implemented according to the project plan and to document any adjustments and/or adaptations	a. At intervention sites, what is the proportion of MWHs that meet each component of the Core Model? b. What proportion of intervention sites are operating according to the project standard operating procedures?	**Quantitative** MWH Register Others Register MWH Activity Log MWH Experience Survey Core Model Checklist **Qualitative** Project records
2. To identify barriers and facilitators to implementation of the interventions	a. What are the barriers and facilitators to implementation of the: 1. Core Model? 2. Governance and management models? 3. IGAs?	**Qualitative** IDI with MWH governance and management structures IDI with IGA staff/volunteers IDI with health facility/system staff
3 To assess the extent to which implementation of the Core Model is perceived as responsive to community standards of acceptability by both the community and the women.	a. How does satisfaction with staying at the MWH compare in intervention sites relative to control sites? b. To what degree are the intervention MWH perceived as responsive to community standards and needs? c. What are the essential features and characteristic of the MWH as perceived by both women and communities? d. What are continued barriers to accessing and utilizing MWH after the intervention?	**Quantitative** MWH Experience Survey **Qualitative** IDIs with MWH governance and management structures FGDs with pregnant/ recently delivered women (RDW), men with children < 1, community el ders, Safe Motherhood Action Group members (S MAGs)
4. To assess the ways in which health facility-level factors change over the course of implementation.	a. How does capacity to handle obstetric emergencies change over time at the facility? b. How do staff perceptions of care related to maternal health change over time? c. What role does the MWH have in shaping staff perceptions of maternal health care?	**Quantitative** Health Facility Assessment **Qualitative** IDI with health facility/system staff

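### The only planned summary of fidelity and facility capacity is a met/not-met proportion over 10 sites per arm; a graded site-level measure should be added

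*Protocol article*

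**What the plan says.** All references are to the protocol article.

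- **Objective.** Objective 1 under Aim and objectives is "To assess the degree to which each intervention component is implemented according to the project plan". Table 2 turns it into two questions about intervention sites: "what is the proportion of MWHs that meet each component of the Core Model" and "What proportion of intervention sites are operating according to the project standard operating procedures".
- **Purpose of the checklist.** The Objective 1 text under Data collection activities says the monthly checklist is to establish how far each site puts the elements of the Core Model into practice, and how standard of care compares at control sites. It uses the same elements as the MWH Experience Survey so that the two can be compared.
- **Purpose of the facility assessment.** The Objective 4 text says facility capacity will be followed over time and its changes related to demand. The tool covers beds, staff, procedures performed and stock outs.
- **Planned analysis.** For the checklist: "the Core Model Checklist will be analyzed to determine the proportion of sites meeting Core Model domain requirements". For the facility tool: "The Health Facility Assessment will be analyzed to determine proportion of sites meeting the standards for signal functions and staffing". Then: "Data will be stratified by intervention and control as well as district/province and compared over time". No rule for a met requirement is given, and no test is named for either tool.
- **Use of the results.** The Discussion wants to learn how differences in implementation affect the trial's outcomes.
- **Size.** There are 10 intervention sites and "the matched control sites (n = 10").

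**The concern.** The stated purposes call for a graded quantity at each site: how many elements are in place, how much capacity there is, and how both move over time. The stated analysis gives one yes or no per site and domain, summed over 10 sites. Two sites on the same side of the cut-off look identical however far apart they are, and a change that does not cross the cut-off does not register.

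Three uses of the data suffer:

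- **Sustainability.** Follow-up after support ends is only about 4 months, so early erosion is likely to be partial.
- **Capacity and demand.** A status that rarely changes at a site leaves little to relate to changes in demand.
- **Interpreting the trial.** If most intervention sites share the same status, there is little variation in implementation to set against outcomes.

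**Working it through.** The article gives no precision or power figure for either tool, so there is none to reproduce. What follows is derived from 10 sites per arm.

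**1. Resolution.** One site is 1/10 = 10 percentage points. The plan also stratifies by district and province. Four districts give an average of 10/4 = 2.5 sites per arm per district; actual district counts are not stated.

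**2. Precision in one arm.** The exact 95% interval for x of n runs from the 0.025 quantile of Beta(x, n−x+1) to the 0.975 quantile of Beta(x+1, n−x). With n = 10:

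| Sites meeting | Exact 95% interval |
|---|---|
| 5/10 | 0.187 to 0.813 |
| 8/10 | 0.444 to 0.975 |
| 10/10 | 0.692 to 1 |

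**3. What the cut-off hides.** Table 1 lists nine infrastructure features. If met means at least k of 9, all scores from k to 9 are recorded alike, and so are all scores from 0 to k−1. If k = 9 (an assumption), a home with eight features counts the same as a home with none. With k below 9, a fall from nine features to k is invisible. For capacity, one of the two eligibility routes in Study setting was a threshold on "signal functions (five out of seven"). If the analysis standard were the same threshold (an assumption), 5, 6 and 7 functions would count alike, and sites that entered by that route would have met it at selection.

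**4. Contrast between arms (illustration).** Assume Fisher's exact test, two-sided alpha 0.05 and a single cross-section of 10 v 10. For p < 0.05 the intervention arm needs at least 5/10 against 0/10, 7/10 against 1/10, 8/10 against 2/10, or 9/10 against 3/10. Exact power is the sum of Bin(a; 10, p1) × Bin(b; 10, p2) over all pairs (a, b) with p < 0.05:

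- 60% v 20%: 0.253
- 80% v 20%: 0.635
- 90% v 10%: 0.958

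A very large contrast would show; a partial one mostly would not.

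**5. Score against dichotomy (illustration).** Assume normal site scores and a true shift of d SD. On the score, a two-sample t-test has 18 df and noncentrality d × √(10/2); for d = 1 this is 2.24. After dichotomising at a cut c, measured in SD above the control mean, the pass rates are 1 − Φ(c − d) and 1 − Φ(c). With d = 1 and c = 0.5 these are 0.69 and 0.31.

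| Shift d | Power, score | Power, cut at either arm mean | Power, cut midway | Power, cut 1 SD above intervention mean |
|---|---|---|---|---|
| 1.0 | 0.562 | 0.185 | 0.219 | 0.010 |
| 1.5 | 0.887 | 0.380 | 0.520 | 0.012 |
| 2.0 | 0.988 | 0.528 | 0.803 | 0.012 |

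**6. Repeated months.** The checklist is monthly. If it runs 24 to 36 months (an assumption; Table 4 uses these lengths for the Experience Survey and the record review), 20 sites give 20 × 24 = 480 to 20 × 36 = 720 site-months. These still come from only 20 independent sites in 10 matched pairs. Steps 4 and 5 ignore both repetition and pairing.

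**The case against.** The strongest reply is that the protocol chose a proportion deliberately. Table 2 words both Objective 1 questions as proportions of sites, and the planned checklist analysis answers the first directly. That stands, and it is why the proportion should stay.

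A reader might infer that the element-level data are thrown away and that the degree of implementation therefore cannot be shown. The article supports neither inference. It does not say that element results will go unreported, and scoring rules and item tables may sit in the full protocol or an analysis plan. Objective 1 also draws on the Experience Survey, which records availability, use and perceived quality by element, and on project records.

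Four further limits stand:

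- Facility capacity belongs to Objective 4, so the argument there rests on the capacity-and-demand aim, not on Objective 1.
- The eight-of-nine example and the signal-function ceiling depend on cut-offs the article does not define, and a second eligibility route did not use the signal-function threshold.
- The section names no test, and question 1a is descriptive and concerns intervention sites, so low power between arms is not in itself a failure of the plan.
- Nothing says the met/not-met status will serve as an exposure in a model of outcomes.

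What the reply does not meet is the gap within the article. The Objective 1 text, the Objective 4 text and the Discussion each need graded site-level information, and the one analysis stated for these tools does not provide it.

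**Conclusion.** The planned proportions are a legitimate answer to question 1a but a coarse one to the wider purposes the article sets. The firm figures rest only on 10 sites per arm: 10-point steps, and an interval as wide as 44% to 97% for 8 of 10. Whether partial loss of fidelity would be missed depends on the undefined rule for met.

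The power comparison (about 56% against about 20% for a 1 SD shift) rests on assumed normality, effect size, cut-off, test and a single cross-section. It shows the direction and rough scale of the loss and is not an estimate for this study. It should not be read as showing that the study is underpowered, since the article plans no such test. Nor does the score rescue a small contrast: 56% is itself modest. This is a worthwhile, inexpensive improvement to a stated analysis.

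**What to change.** In the analysis section on the health facility assessment and checklist:

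1. Keep the proportions of sites for question 1a, and state how many elements make a domain requirement met and which signal-function and staffing standards apply.
2. Add, per site and month, the percentage of applicable Core Model elements met, overall and by domain. Fix in advance which elements count as applicable at control sites, since some of those facilities have no waiting structure.
3. Add the number of signal functions performed (0 to 7) as the graded capacity measure for Objective 4.
4. Compare both measures between arms and over time with the site as the unit, allowing for matched pairs and repeated months. Examples are within-pair differences in site averages over fixed periods, or a mixed model with pair and site effects and a small-sample correction. Show the period after support ends separately.
5. Use the site scores when relating capacity to demand and implementation to outcomes.

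The checklist and facility data are already collected monthly, so the cost is a few lines of analysis text and a scoring rule.

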### Qualitative analysis

Since we are using a repeated cross-sectional samples design, we will analyze each wave of data first, then analyze themes over time, connecting what has changed and how these changes might have occurred. We will conduct a content analysis of the IDI transcripts. Codes have been identified a priori according to the outline of the interview guides. We will then derive meaning from the coded data using the following steps: 1) familiarization; 2) identifying a thematic framework; 3) indexing; 4) charting; and 5) mapping and interpretation [23]. Qualitative data from IDIs and FGDs will be analyzed against the community-defined standards of acceptability from the formative evaluation [9]. Additional themes will be included if they emerge during analysis. Stratified by intervention and control site, we will review qualitative and quantitative data together to understand acceptability as measured by implementation fidelity of the Core Model, and findings from the impact evaluation.

## Ethics and dissemination

This study protocol received ethical approvals from the Boston University Medical Campus Institutional Review Board (IRB) and the ERES Converge IRB in Zambia. Written informed consent will be obtained by study staff and documented through signatures for all interviews and surveys. If the respondent is unable to provide a signature, the respondent will provide a thumbprint and an impartial, literate witness will sign as well after witnessing the informed consent process. Informed consent will not be obtained for the data extracted from the registers. The study staff ensures extracted data are kept private and confidential, and that they are de-identified as soon as women are linked across registers using the SMN number. Any adverse events and unanticipated problems will be reported to the in-country project director and communicated to the principal investigator. All adverse events and unanticipated problems will be reported to the ethical boards per policy and the protocol will be amended if necessary. Results will be disseminated among key stakeholders in Zambia, then through appropriate open-access channels.

## Discussion

Alongside the impact results of the cRCT, the findings from this implementation effectiveness and sustainability evaluation will be analyzed in order to interpret outcomes, identify mechanisms of impact and understand how variations in implementation affect these outcomes. We also aim to provide evidence of factors that may improve longer-term sustainability of MWH in this context. Results will be combined with detailed costing data being collected concurrently in order to also understand cost outcomes and cost-effectiveness. We aim to disseminate the combined results to donors, policymakers and program implementers in order to facilitate their future decision-making regarding the implementation of MWHs in Zambia. Results may be used as evidence for programmatic decisions by the government and supporting agencies in deciding to take this model to scale beyond the districts proposed for this project and to continue routine implementation of the model beyond the MAHMAZ project. In addition, this protocol may provide a guide for other researchers and evaluators to implement similar studies to assess implementation effectiveness and sustainability alongside more complex RCTs or quasi-experimental studies of program outcomes.

## Data Availability

The datasets used and analyzed during the current study are available from the corresponding author on reasonable request.

## Abbreviations

Africare/UM: Africare/University of Michigan
BEmONC: Basic emergency obstetric and newborn care
BU/RTC: Boston University/Right to Care Zambia
CEmONC: Comprehensive emergency obstetric and newborn care
CFIR: The consolidated framework for intervention research
cRCT: Cluster-randomized controlled trial
FGD: Focus group discussion
GRZ: Government of the Republic of Zambia
IDI: In-depth interview
IGA: Income generating activities
IRB: Institutional Review Board
M&E: Monitoring and Evaluation
MAHMAZ: Maternity Homes Access in Zambia Project
MHA: Maternity Homes Alliance
MoH: Ministry of Health
MSD: Merck Sharp and Dohme
MWH: Maternity waiting home
RDW: Recently delivered women
SMAG: Safe Motherhood Action Group
SMN: Safe motherhood number
SOP: Standard operating procedure
WHO: World Health Organization
